### Measures

Primary and secondary outcome measures along with covariates are described in Table 1. Primary outcomes include DBS-assessed viral suppression, ART adherence, health-related quality of life, and depressive symptoms. The secondary outcomes are potential mediators of intervention effects, including social support, loneliness, internalized HIV stigma, general self-efficacy, treatment adherence self-efficacy, social and medical service use, and structural barriers (such as transportation as a barrier to care and housing instability). All primary and secondary outcomes are assessed in each survey (at baseline and 4, 8, and 12 mo) except for viral suppression, which is assessed via DBS at baseline and 4 and 12 months. Covariates are variables that will be controlled for in outcome analyses should they differ across randomized conditions or be associated with retention. We also include measures of feasibility and acceptability in the 4-month survey.

**Table 1 table1:** Study measures.

Domains and subdomains			Description or scale
**Primary outcomes (baseline and 4, 8, and 12 mo)**			
	Viral suppression	Measured viral load <839 copies/mL in HemaSpot (Spot On Sciences) DBS^a^ sample (baseline and 4 and 12 mo only)	
	ART^b^ adherence	Wilson adherence scale [39] scores recoded to indicate imperfect vs perfect adherence, as suggested in the literature [40]	
	Quality of life	Scale score (0-100) on the WHOQOL-HIV BREF^c^ [41], calculated as in the study by Walsh et al [21]	
	Depressive symptoms	Scale score (0-27) on the PHQ-9^d^ depression module [42]	
**Secondary outcomes (baseline and 4, 8, and 12 mo)**			
	Social support	Scale score (1-5) on the MOS^e^ social support survey [43]	
	Loneliness	Scale score (1-5) on the loneliness survey from the NIH^f^ Toolbox [44]	
	Internalized HIV stigma	Scale score (1-5) on the internalized stigma subscale of the HIV Stigma Mechanisms Scale [45]	
	General self-efficacy	Scale score (1-5) on the New General Self-Efficacy Scale [46]	
	Treatment adherence self-efficacy	Scale score (0-4) on the HIV-ASES^g^ [47]	
	Service use	Participants will report which of 12 HIV-related social and medical services they have needed during the previous 3 mo and which of these needed services they were able to obtain [48]; a composite variable will indicate whether participants successfully accessed at least 1 needed service (0=no, 1=yes)	
	Structural barriers	Participants will report barriers faced in the past 3 mo, with items assessing the following: not having current health insurance, transportation as a barrier to health care, finances as a barrier to health care, not having enough food to eat, not having stable housing, and lacking eHealth literacy; the number of barriers will be summed (scores 0-6)	
**Covariates (baseline)**			
	Demographics, socioeconomic position, and health	Age, sex, gender identity, sexual orientation, race and ethnicity, education, income, employment, insurance status, years living with HIV, number of comorbid health conditions, and mode of survey completion (web-based vs paper)	
	Geography	State of residence and Index of Relative Rurality [38,49]	
	Use of other services	Use of HIV case management and participation in other social support groups	
**Acceptability and feasibility (4 mo)**			
	Acceptability of interventions	Satisfaction with interventions [50,51]	
	Acceptability of DBS testing	HemaSpot usability and acceptability questions [52]	
	Session attendance	Tracked by study staff	

^a^DBS: dried blood spot.

^b^ART: antiretroviral therapy.

^c^WHOQOL-HIV BREF: World Health Organization Quality of Life–HIV questionnaire short version.

^d^PHQ-9: Patient Health Questionnaire-9.

^e^MOS: Medical Outcomes Study.

^f^NIH: National Institutes of Health.

^g^HIV-ASES: HIV Treatment Adherence Self-Efficacy Scale.

### HIV Viral Load Testing

At enrollment, 4 months, and 12 months, participants will be sent a DBS kit by US Postal Service to self-collect a blood sample for HIV viral load testing. The DBS kits contain a HemaSpot collection device (volume capacity 80 μL); alcohol pads; 2 single-use retractable safety lancets; gauze pads; bandages; a biohazard bag labeled with participant ID; a postage-paid envelope for specimen return; and an instruwction card, written at an eighth-grade reading level, that describes how to collect the specimen. Participants are instructed to call study staff if they need additional assistance while collecting their samples. Participants will return specimens directly to the clinical laboratory for testing using a preaddressed shipping envelope. Shipping will be tracked by the study team, and specimen arrival will be logged by the laboratory.

HemaSpot devices with sufficient blood volume will be tested using the automated Abbott m2000 platform and the RealTime HIV-1 DBS reverse transcription polymerase chain reaction assay [53]. The assay has a limit of detection (LOD) of 2.92 log copies/mL (839 copies/mL) and can quantify up to 7.0 log copies/mL [54]. When no HIV-1 RNA is detected, the laboratory will report a result of “not detected” or “undetectable.” Detectable specimens will be binarized into qualitative and quantitative results based on the LOD. Qualitative viral load results will include those detectable but not quantifiable, as they fall below the LOD of 839 copies/mL. The laboratory will report quantitative viral load results when HIV-1 RNA is both detectable and quantifiable (≥839 copies/mL). The primary outcome of viral suppression will be defined as a viral load of <839 copies/mL.

Self-collection of DBS specimens for viral load monitoring was shown to be highly feasible and acceptable in our pilot work with older rural people living with HIV [21].

### Sample Size

With the recruitment of a sample size of 352 participants and anticipated 80% retention over time, tests for effects of the interventions will have a power of 0.80 or greater for a type I error of 0.05 to detect a difference of 0.35 SDs in the mean quality of life and depressive symptoms and of 35% in ART adherence and viral suppression between participants receiving versus not receiving each intervention at each follow-up assessment. A higher retention rate will increase power to detect smaller effects.

### Statistical Analysis

We will describe demographic characteristics for the sample and baseline levels of all primary and secondary outcomes. We will use ANOVA and chi-square tests to assess baseline differences in demographics and outcomes for those assigned to the 4 conditions. If significant differences between conditions exist, these will be accounted for in the primary analyses. Finally, we will assess possible sample attrition bias by examining demographic characteristics associated with loss to follow-up and by comparing retention across the 4 conditions.

We will use an intent-to-treat approach when analyzing outcomes [55]. The focus will be on the main effects of each intervention. We will use generalized linear mixed models (GLMMs) to test the impact of each intervention on the primary outcomes of viral suppression, ART adherence, quality of life, and depressive symptoms over time. This approach will test hypotheses within a repeated measures framework, with an individual identifier included in the models as a random effect to account for the correlation between participants’ outcomes over time. We will test hypotheses that the social support intervention and the SBCM intervention increase the likelihood of viral suppression and ART adherence, improve quality of life, and reduce depressive symptoms at 4-, 8-, and 12-month follow-ups, compared to not receiving each intervention, by examining the main effect of each intervention. The impact on viral suppression will be evaluated at 4 and 12 months only. GLMMs will also test the 2-way interaction between the interventions to understand whether the interventions are enhanced or offset by one another. If any differences between the randomized conditions emerge in preliminary analyses, covariates will be included in the models to account for these differences; similarly, if any covariates are associated with retention in the study, these covariates will be included in the models to improve the handling of missing data. Separate GLMMs will evaluate each hypothesis, with appropriate link functions used for binary outcomes (viral suppression and adherence) and continuous outcomes (quality of life and depressive symptoms). Hypotheses will be tested at the *P*<.05 level.

The same approach will be used to test the impact of each intervention on the secondary outcomes of social support, loneliness, stigma, self-efficacy, service use, and structural barriers. We will test hypotheses that the social support intervention and the SBCM intervention increase social support, self-efficacy, and uptake of needed services as well as decrease loneliness, stigma, and structural barriers at 4-, 8-, and 12-month follow-ups, compared to not receiving each intervention, by examining the main effect of each intervention.

Exploratory analyses will assess whether intervention effects differ based on demographic characteristics—including sex, race, and age (age 50-64 y vs age >65 y)—and baseline engagement in care (low vs high). Moderation analyses will shed light on who most benefits from the intervention programs, which can help guide better targeting of the programs or future efforts to refine and tailor interventions to meet the needs of any who do not benefit. We will test moderation by introducing interaction terms into the GLMM models assessing primary and secondary outcomes. In separate models for each moderator and outcome, we will include interactions between the moderator and assignment to each intervention as predictors of outcomes. Significant interaction terms will indicate differing intervention effects across subgroups. Significant interaction terms will be “plotted and probed” to examine intervention effects within different subgroups of participants [56].

Additional exploratory analyses will test whether the amount of each intervention received (ie, the number of sessions attended) or the mode of intervention delivery (ie, Zoom [Zoom Video Communications, Inc] vs telephone) relate to outcomes. These analyses will include only those participants randomly assigned to receive each intervention. GLMM models will examine associations between the number of intervention sessions attended or mode of intervention delivery (predictors) and outcomes (viral suppression, ART adherence, quality of life, and depressive symptoms), controlling for demographic covariates as needed. Separate models will estimate dose-response and mode-response relationships for each intervention-outcome combination.

Finally, analyses will explore the mediators of intervention effects on outcomes to shed light on the potential mechanisms of intervention effects. Understanding mediating mechanisms can help guide future efforts to optimize programs by capitalizing on the key processes involved in generating health outcomes. Mediation will be tested in a structural equation model, which will be fit in Mplus (Muthén & Muthén) [57] using a full-information maximum likelihood estimator robust to nonnormality. The model will include effect-coded interventions as predictors; social support, loneliness, self-efficacy, service use, and structural barriers as mediators; and viral suppression, adherence, quality of life, and depressive symptoms as outcomes. For a longitudinal test of mediation, models will include mediators assessed at 4 months and outcomes assessed at 8 and 12 months. Paths will lead from interventions to all mediators and from all mediators to all outcomes. Residual correlations between different mediators and different outcomes will be allowed, and covariates will be included as needed. Although we anticipate specific mechanisms for each intervention, this method will allow for a complete understanding of the mechanisms. We will use bootstrapped CIs to assess the indirect effects of the interventions on outcomes via mediators.

To inform future intervention implementation, we will also summarize information related to the acceptability and feasibility of each intervention and of the HemaSpot DBS testing for viral load. Acceptability will be assessed by survey items (Table 1). In terms of feasibility, we will summarize participation in each intervention (eg, number of sessions attended).

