### Procedures

Participants will be screened for eligibility using a web-based screener or by telephone. Study flyers contain the study web page, QR code, and our study telephone number. Online advertisements and postings contain a direct link to the screener. Study staff will contact eligible participants by telephone to describe the study, review the main components of the consent, and answer questions. Participants interested in enrolling will be sent either (1) a link to the web-based informed consent document and baseline survey by email or SMS text message or (2) a packet containing the informed consent document, baseline survey, and a stamped and addressed envelope for survey return via US mail. All participants interested in enrolling will also be sent a DBS study kit via US mail (refer to the HIV Viral Load Testing subsection). To guard against duplicate and fraudulent enrollments, we will require a unique and valid telephone number and postal address for each participant and speak with each participant before enrollment.

Only eligible participants who enroll in the study, complete a baseline survey, and return the baseline DBS study kit to the laboratory will be randomly assigned (refer to the Randomization subsection). After assignment, participants will be offered 0, 1, or 2 remote interventions depending on group (refer to the Interventions subsection). These interventions will be delivered over 5 to 8 weeks. Participants will complete follow-up assessments at 4, 8, and 12 months after assignment and provide DBS specimens at 4 and 12 months after assignment.

We will maximize retention by collecting multiple types of contact information (eg, telephone numbers, email address, and postal address) from participants upon enrollment. We will maximize participation in intervention sessions by providing reminders before each session using each participant’s preferred method of communication and by providing a modest compensation for each core intervention session attended.

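### The attrition check and the retention-covariate rule leave out the baseline primary outcomes, so loss related to them, or related differently by condition, would go undetected; the likely bias is modest if each model includes its own baseline.

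*Protocol article*

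**What the plan says.** The Statistical Analysis section of the protocol article has two provisions on loss to follow-up.

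- **Diagnostic:** "we will assess possible sample attrition bias by examining demographic characteristics associated with loss to follow-up and by comparing retention across the 4 conditions".
- **Correction:** "if any covariates are associated with retention in the study, these covariates will be included in the models to improve the handling of missing data".

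The Measures section defines the term used in the second: "Covariates are variables that will be controlled for in outcome analyses should they differ across randomized conditions or be associated with retention". Table 1 then lists the covariates in three groups:
- demographics, socioeconomic position and health, beginning "Age, sex, gender identity, sexual orientation, race and ethnicity, education, income" and going on to years with HIV, comorbidity count and survey mode;
- geography;
- other services: "Use of HIV case management and participation in other social support groups".

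The four primary outcomes appear in Table 1 as outcomes, not as covariates. Their baseline values are compared between the four conditions, but no comparison of retained with lost participants is stated for them.

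The values will be at hand. Under Procedures, the participants who are randomised are "Only eligible participants who enroll in the study, complete a baseline survey, and return the baseline DBS study kit to the laboratory".

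The outcome model is a repeated-measures generalized linear mixed model (GLMM) with a participant random effect. The article does not say whether the baseline value is a response row or a covariate. The Sample Size section anticipates 80% retention of 352 participants.

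**The concern.** Poor viral control, poor adherence and depression are plausible reasons for leaving a study such as this one, and they predict later outcomes. The diagnostic does not look at them, and the correction rule draws on a list that omits them.

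The comparison of retention across conditions does not fill the gap. Two conditions can each keep 80% of their participants while losing different kinds of people. Assignment is unblinded, and the conditions range from mailed information alone to eight group sessions plus up to five individual ones, so this cannot be ruled out. No test of whether predictors of loss differ by condition is stated.

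At stake is a reassuring report on attrition that the check cannot support, and some bias in the main effects that data already collected could remove.

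**Working it through.** **1. The plan's own figure.** Each main effect compares halves of the sample, so 352 × 0.80 / 2 = 140.8 retained per level. Power for 0.35 SD at two-sided 0.05 (sidedness assumed) is Φ(0.35 × √(140.8/2) − 1.96) = Φ(2.94 − 1.96) = 0.836. The stated power of at least 0.80 holds, and 0.35 SD is a fair yardstick for bias. Expected losses are 0.20 × 352 ≈ 70.

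**2. Can equal retention hide bias? Viral suppression.** All inputs are assumed: 85% suppressed at baseline; later suppression 95% if suppressed at baseline and 40% if not; no intervention effect; 80% retained in both groups. Let ru and rs be retention of the unsuppressed and the suppressed, with 0.85·rs + 0.15·ru = 0.80. Among completers, the share suppressed at baseline is s = 0.85·rs / 0.80, and later suppression is 0.95·s + 0.40·(1 − s).

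| ru | rs | s | later suppression | OR vs even loss |
|---|---|---|---|---|
| 0.80 | 0.800 | 0.850 | 86.8% | 1.00 |
| 0.60 | 0.835 | 0.888 | 88.8% | 1.21 |
| 0.50 | 0.853 | 0.906 | 89.8% | 1.35 |

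These are crude completer comparisons. Within each baseline stratum the groups are identical (95% and 40%), so conditioning on baseline suppression removes the bias entirely.

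**3. Loss driven by the outcome's own baseline, continuous outcome.** Null simulation with 176 per level, 20% expected loss in each, and a completer comparison at one follow-up. Assumed: baseline to follow-up correlation 0.5 or 0.7, and dropout logistic in the baseline value with the log-odds per SD shown.

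| Dropout slopes in the two levels | Bias without baseline (SD) | Type I error | Bias with baseline (SD) | Type I error |
|---|---|---|---|---|
| 0.5 and 0.5 | about 0 | about 0.05 | about 0 | about 0.05 |
| 0.7 or 1.0, and 0 | 0.07 to 0.12 | 0.10 to 0.19 | about 0 | about 0.05 |
| 0.7 and −0.7 | 0.13 to 0.18 | 0.20 to 0.35 | about 0 | 0.05 to 0.06 |

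Biases are absolute values. Without baseline, the range 0.07 to 0.18 SD is 20% to 52% of 0.35 SD (0.07/0.35 and 0.183/0.35).

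**4. Loss driven by another outcome's baseline.** Null simulation, 352 participants, 80% retained in each level, quality of life missing according to baseline depression, assumed correlations 0.45 to 0.6.

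| Model | Bias, slopes 0.7 and −0.7 (SD) | False positives |
|---|---|---|
| No baseline | 0.12 to 0.13 | 16% to 20% |
| Baseline quality of life | 0.04 to 0.05 | about 7% |
| Baseline quality of life and depression | 0 | 5% |

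With a slope in one level only, the residual after baseline quality of life is 0.02 to 0.03 SD (about 6% false positives). The residual range of 0.02 to 0.05 SD is 6% to 14% of 0.35 SD. Only adding baseline depression removes it, and the stated rule does not provide for that.

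**The case against.** The strongest reply is that the main protection lies in the model, not in the descriptive check. If the GLMM contains the baseline value, loss driven by that outcome's own baseline is handled under missing-at-random, even when it differs by condition. Step 3 confirms this. It also shows no bias when loss depends on baseline equally in both levels. This stands, and it confines the point to loss driven by other outcomes.

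It is also fair that nothing in the article shows that viral load, adherence or depression drives dropout here. Surveys, DBS kits and their payments are the same in every condition, and missing a session is not loss to follow-up. The drivers are assumptions.

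Three stronger readings are not supported:

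- **That only demographics are considered and loss goes uncorrected.** The correction rule covers every Table 1 covariate, including comorbidity, years with HIV, geography and service use. Only the baseline outcomes are missing.
- **That odds ratios of 1.21 to 1.35, or biases of 0.07 to 0.18 SD, are the expected size.** They hold only if baseline is left out, and the article leaves that open.
- **That the plan treats survey and specimen loss as one event.** The article does not define loss to follow-up at that level, a detail that may sit in a fuller document. Separate checks are part of the remedy, not evidence of an error.

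Finally, crossing every predictor with all four conditions would be too heavy. The four baseline measures alone would need 4 × 3 = 12 interaction terms on about 70 losses, before any demographic. The remedy is cut back accordingly.

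**Conclusion.** The point holds in a limited form. The stated check would not detect loss related to the baseline primary outcomes, or related to them differently by condition, and the stated rule would not bring those measures into the models. This follows from the text and needs no assumption.

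The size of the bias does rest on assumptions. If each model includes its own baseline, the main exposure is loss driven by another outcome's baseline that differs by condition. For quality of life this is about 0.02 to 0.05 SD, with false positives of about 6% to 7% instead of 5%. The simulations are completer regressions at one follow-up with assumed correlations and dropout slopes, not fits of the planned GLMM. No comparable figure was worked out for depression driving missing viral load.

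This is a minor to moderate improvement, worth making because the data are already collected.

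**What to change.** Reword the two provisions in the Statistical Analysis section:

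1. Extend the attrition check to baseline viral suppression, adherence, quality of life and depressive symptoms, alongside the demographic characteristics.
2. Run it separately for missing surveys and missing DBS results.
3. Add interactions of these four measures with each of the two intervention factors, 4 × 2 = 8 terms, and not with all four conditions or all demographics. With about 70 losses, take one measure at a time and report estimates with intervals instead of relying on significance.
4. Make the four baseline measures eligible retention covariates, so that those related to loss enter the models for the other outcomes.
5. State how each outcome's own baseline enters its GLMM: once, either as a response row or as a covariate.

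The cost is a change of wording, a short extra analysis and a few more model terms. No new data are needed.

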#### Supportive-Expressive Peer Social Support Groups Intervention

This program, adapted from Project Linkage [25], is delivered to groups of approximately 8 to 12 participants by trained facilitators from the Southern AIDS Coalition. The groups meet weekly for 90-minute sessions over 8 weeks. Participants may choose to join each session by videoconference with or without video, or they may join by telephone for an audio-only experience. Each session has a unique focus: (1) introductions, program overview, and establishing group rules and expectations; (2) feelings around HIV diagnosis, stigma, and questions of “why did HIV happen to me?”; (3) values and priorities in life and thoughts about mortality; (4) uncertainty, challenges, and lack of control; (5) physician-patient relationship; (6) friend and family relationships; (7) body image and sense of self; and (8) reflection, summary, and closure. On the basis of participant feedback during our pilot, we incorporated the topic of HIV-related stigma into this intervention and also recruited group facilitators who had more shared lived experiences with participants. After the 8 group meetings, participants in groups are offered the opportunity to share their contact information with other participants if they are interested and sent instructions on how to host their own videoconference meetings should they wish to continue meeting to provide mutual social support.

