### Randomization

Participants will be randomly assigned to 1 of 4 conditions in a 2 (social support groups: yes or no) × 2 (SBCM: yes or no) between-participants factorial design. Randomization will occur on an individual basis using the REDCap (Research Electronic Data Capture; Vanderbilt University) randomization module. An equal number of participants will be randomly assigned to each condition. Randomization will occur in blocks of 8 and be stratified based on sex. Neither participants nor study staff will be blinded to condition assignment.

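### The primary model has no term for the peer groups in which half the sample is treated, so the support-group test is anti-conservative if outcomes correlate within groups

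*Protocol article*

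**What the plan says.** **Allocation.** The Randomization section randomizes individuals to four conditions: "An equal number of participants will be randomly assigned to each condition". Two of the four include the support groups, so half of 352, or 176 people, are assigned to them.

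**Delivery.** The support intervention "is delivered to groups of approximately 8 to 12 participants by trained facilitators from the Southern AIDS Coalition", in eight weekly 90-minute sessions. Members are then offered the chance to exchange contact details and are told how to go on meeting.

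**Model.** Statistical Analysis specifies generalized linear mixed models "with an individual identifier included in the models as a random effect to account for the correlation between" one person's repeated measurements. The secondary outcomes use the same approach. Neither support-group membership nor facilitator appears anywhere in the analysis.

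**Power.** Sample Size makes one statement for both interventions: "tests for effects of the interventions will have a power of 0.80 or greater". It rests on 352 recruited, 80% retained and a 5% type I error. The target is 0.35 SD on the two continuous primary outcomes and 35% on the two binary ones, at every follow-up visit. No ICC, group size or design effect is given.

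**The concern.** The design is partially nested: the two support-group conditions contain treatment groups and the other two do not. The intervention is meant to work through exchange among members (support, loneliness, stigma), so people in the same group may end up more alike than people in different groups. A participant random effect handles repeated measures within a person. It leaves two members of the same group independent.

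If there is positive correlation within groups, the variance of the support-group mean is understated. A support intervention with no effect would then be declared effective more often than the stated 5%, and its confidence intervals would be too narrow. The power given for that intervention would also be too favourable. It is one of only two interventions under test.

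**Working it through.** **Inputs from the article.** N = 352; retention 80%; 1:1:1:1 allocation; group size about 8 to 12; 0.35 SD; type I error 0.05 (taken as two-sided).
- Retained per level of each factor: 352 × 0.80 / 2 = 140.8.
- Number of groups: 176/12 = 14.7 to 176/8 = 22.

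**Assumed, because the article gives no value.** ICC of 0.01 to 0.10. Central case m = 8 analysed per group (10 × 0.80).

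**1. Reproducing the stated power.** Under independence SE = √(2/140.8) = 0.1192 SD. Power = Φ(0.35/0.1192 − 1.96) = 0.836. This agrees with the stated 0.80 or greater, and it treats every participant as independent.

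**2. Adding group clustering on one side only.**
- DEFF = 1 + (m − 1) × ICC
- SE = √((1 + DEFF)/140.8)
- SE ratio R = √((1 + DEFF)/2)
- Actual type I error of the participant-only test = 2(1 − Φ(1.96/R))
- Valid power = Φ(0.35/SE − 1.96)
- Detectable difference at 80% power = 2.802 × SE

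| ICC (m = 8) | DEFF | R | Type I error | Valid power | Detectable difference |
|---|---|---|---|---|---|
| 0.01 | 1.07 | 1.017 | 5.4% | 0.82 | 0.340 SD |
| 0.02 | 1.14 | 1.034 | 5.8% | 0.81 | 0.345 SD |
| 0.05 | 1.35 | 1.084 | 7.1% | 0.77 | 0.362 SD |
| 0.10 | 1.70 | 1.162 | 9.2% | 0.72 | 0.388 SD |

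Larger groups at ICC 0.10:
- m = 9.6 (12 × 0.80): 10.1% and 0.69.
- m = 12: 11.5% and 0.66. This is an outer bound, since it assumes no loss within groups while still using 140.8 retained.

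**3. Where 0.80 is lost.** Power is 0.80 when 1 + DEFF = 140.8 × (0.35/2.802)² = 2.197, so ICC = 0.197/(m − 1). That is 0.037 for m = 6.4 (8 × 0.80), 0.028 for m = 8, 0.023 for m = 9.6 and 0.018 for m = 12.

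**4. Main effect over three visits.** Assume a within-person correlation of 0.6 and a group effect that is constant over visits. A person's mean has variance (1 + 2 × 0.6)/3 = 0.733, and SE = √((2 × 0.733 + (m − 1) × ICC)/140.8).
- Power with m = 8: 0.93 under independence; 0.91, 0.87 and 0.81 at ICC 0.02, 0.05 and 0.10.
- Type I error with m = 8: 5.5% at ICC 0.01 and 10.7% at ICC 0.10. A simulation at the same correlation gave 5.8% and 10.3%.

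Averaging over visits therefore protects power but not the type I error.

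**5. The SBCM main effect and the interaction.** In a balanced 2×2 both contrasts depend on the difference between the two support-group cells, so both have the same SE ratio. If each peer group mixes participants with and without SBCM in equal numbers, the group effect cancels and R = √((2 − ICC)/2), which is 0.975 at ICC 0.10, so neither test is inflated. If groups were formed separately by condition, R would be as in step 2 for both. The article does not say how groups are composed.

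**6. Binary outcomes.** The 35% has no base rate and is not labelled absolute or relative, so no figure can be derived for viral suppression or adherence.

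**The case against.** **The power statement largely survives.** A reader might infer that 0.80 fails as soon as clustering is respected. The figures do not support that. At m = 8 it holds at ICC 0.01 and 0.02, and the three-visit main effect stays above 0.80 up to ICC 0.10. This objection stands.

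**The ICC is assumed.** Participants are individually randomized, come from 17 states and attend remotely, some by audio only. Intent-to-treat keeps non-attenders, which dilutes any group correlation. So it would go too far to state as fact that the standard errors are too small: that follows only if the ICC is positive. This too stands. It limits the size of the problem, but it gives no ground for fixing the ICC at zero.

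**Not every primary test is shown to be affected.** Two of the four primary outcomes are binary and were not quantified. The direction of the bias is the same for them; its size is unknown.

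**The article is condensed.** A fuller analysis plan could name a further variance component. But the article is not silent here: it names the random effect and its purpose, and that purpose omits the dependence its own intervention may create. The objection does not remove the point.

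**Details a reader might supply.** The article does not say that groups are closed, that each has a single facilitator, or that group membership is known for everyone. The argument needs only that members share sessions.

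**Conclusion.** The point holds in a limited form. As written, the model for the support-group main effect ignores a source of dependence created by group delivery, and its tests and intervals are anti-conservative for any positive within-group correlation. For an assumed ICC of 0.01 to 0.10 and 8 analysed per group, single-visit type I error on quality of life and depressive symptoms is about 5.4% to 9.2% (up to 11.5% with 12 per group). Valid single-visit power at 0.35 SD is about 0.82 down to 0.72 (0.66 with 12 per group). These are normal approximations; with only 15 to 22 groups, small-sample degrees of freedom would lower power somewhat further.

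The stated 0.80 fails only above an ICC of about 0.02 to 0.04, depending on group size. SBCM is delivered one to one, and its main effect should be little affected if peer groups mix the SBCM conditions. The interaction test is anti-conservative as well if groups are formed separately by condition. The article does not show that the stated power is wrong, nor that all primary hypotheses are compromised.

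**What to change.** - Fit a partially nested mixed model: keep the participant random effect and add a support-group random effect that applies only in the two support-group conditions.
- For the continuous outcomes, use Satterthwaite or Kenward-Roger degrees of freedom.
- Record the scheduled group for each participant assigned to support, whether or not they attend. State how those never scheduled are handled, for example as singleton clusters.
- State whether groups mix participants with and without SBCM.
- Restate power or the detectable difference for the support-group effect with an assumed ICC and group size. With 8 analysed per group it is about 0.345, 0.36 and 0.39 SD at ICC 0.02, 0.05 and 0.10.

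**Cost.** One more variance component, a group identifier in the data and some wording; no extra participants or assessments. Intervals for the support-group effect become slightly wider and its stated power slightly less favourable. Follow-up is planned to end by April 2027, so the change can be made before analysis.
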